### Study outcomes

#### Primary: denture-related stomatitis remission

To evaluate the effect of the hygiene protocols on DS remission, the participants will be examined under the baseline condition and also 10 days after starting their specific use of the protocol. To quantify the inflammation, standardized photographs of the palate will be obtained (Digital Camera, Canon EOS, Canon EF 100 mm/2: 8 Macro Lens and Canon ML3 Circular Flash), with the focus centered on the median raphe region. The images will be transferred to the computer and two blinded, previously trained researchers will assign scores according to the classification of Kabawat et al. [10].

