### Eligibility criteria

#### Inclusion criteria

The inclusion criteria are as follows: (1) patients may be of either sex; (2) patients must have good general health; (3) patients must be without teeth in both arches, users of upper and lower conventional complete prostheses, or, necessarily, users of a complete upper prosthesis (although edentulous mandibular) in good condition [28]; (4) prosthesis must be made from thermally polymerized acrylic resin and acrylic teeth; (5) patients must present with DS types IB, II, or III, according to the Newton Modified Classification [10]; and (6) their prostheses should present with biofilm with a score equal to, or greater than 1, according to Additive Index Exclusion criteria.

The following patients will be excluded: those patients who (1) present with prostheses with adaptation problems, failures, repairs, or fractures; (2) have allergy to any of the products studied; (3) have severe/serious illness that requires frequent hospitalization; (4) have systemic conditions favorable to the development of *Candida* spp.; (5) have used antibiotic, anti-inflammatory, or antifungal agents in the 4 weeks prior to the study; (6) have other lesions on the oral mucosa; (7) are already practicing palatal mucous brushing at recruitment; and (8) use replacement prostheses during the experimental period.

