### Sample size estimation

Sample size for the quantitative outcomes was determined based on the primary outcome of this study (denture-related stomatitis remission). According to a previous trial [11], we used standard deviation of 2.19 (group 1 - saline group) and 1.79 (group 2 - sodium hypochlorite), a 95% confidence interval (bilateral), and a detectable difference of at least 2 logs. Based on power of 80%, this clinical study requires at least 21 participants. An additional 20% will be added to the planned sample to compensate for possible dropouts, thus resulting in a total of 25 participants.

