## Trial status

First version (01) of the study protocol, 22 July 2019.

Second version (02) of the study protocol, 17 October 2019.

Recruitment of patients: Initial date 03 September 2018

This trials is currently analysing clinical results and will initiate the cytokines and MUC1 analyses.

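### The primary outcome is called remission, but only a photographic score is measured, no rule links the two, and the sample size is on a log scale that fits neither

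*Protocol article*

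**What the plan says.** The outcomes section of the protocol article carries the heading "Primary: denture-related stomatitis remission". Its stated aim concerns remission ("To evaluate the effect of the hygiene protocols on DS remission, the participants will be examined under the baseline condition"), with assessment at baseline and day 10. The measurement is a score: "To quantify the inflammation, standardized photographs of the palate will be obtained", after which "two blinded, previously trained researchers will assign scores according to the classification of" a cited reference. No cut-off or rule turns the score into remission.

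The inclusion criteria cite the same reference for the modified Newton classification: "patients must present with DS types IB, II, or III".

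The sample size section says: "Sample size for the quantitative outcomes was determined based on the primary outcome of this study (denture-related stomatitis remission"). Its inputs are standard deviations of 2.19 and 1.79, a difference of at least 2 logs, a two-sided 95% level and 80% power. They give 21 participants, raised to 25 for dropout.

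The statistical analysis section says that group effects on primary and secondary outcomes will be assessed. It names the Brunner-Langer test for non-normal data and ties the Friedman and Kruskal-Wallis tests to categorical questionnaire variables. It gives no test of proportions and nothing specific to the primary outcome. The trial status section reports that the trial is "currently analysing clinical results".

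**The concern.** Remission is a state that a patient either reaches or does not. A classification score is an ordered variable. A quantity with a standard deviation in logs is a third kind of variable. The primary outcome is described in all three ways, and nothing connects them.

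Two things are at stake. The first is meaning: a patient who moves from type III to II, or from IB to a lower type, has improved on the score, but the text does not say whether that patient is in remission. Two analysts could report different primary results from the same photographs. The second is power: the 80% belongs to a log-scale comparison of means, so it says nothing about the chance of detecting a difference in score or in remission.

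**Working it through.** **1. The plan's own figure.** Inputs from the sample size section: SDs 2.19 and 1.79, difference 2, two-sided α = 0.05, power 80%.

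- Pooled SD = √[(2.19² + 1.79²)/2] = 2.00.
- n per group = 2 × SD² × (1.960 + 0.842)² / 2² = 15.7, so 16 (17 with the t distribution).
- The stated 21 is not reproduced. Power of 90% gives 21.0 before rounding, but the text states 80%. The dropout step is 21 × 1.2 = 25.2, reported as 25.

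The mismatch between 16 and 21 is a separate matter, and this point does not depend on it. What matters here is the unit: no variant of this calculation gives a sample size for a proportion or an ordered grade, because the inputs are an SD and a difference in logs. Within the article, the outcome a log scale would fit is the colony-forming unit count, which is secondary.

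**2. The three descriptions side by side.**

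| Place | Description | Type of variable |
|---|---|---|
| Primary outcome, heading and aim | Remission | Binary, no threshold given |
| Primary outcome, measurement | Score from photographs | Ordered |
| Sample size | Difference of 2 logs, SDs 2.19 and 1.79 | Continuous |

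**3. If remission is binary.** The article gives no remission rates, so these are assumptions. For 20% versus 50% in two arms, n = [1.960√(2 × 0.35 × 0.65) + 0.842√(0.20 × 0.80 + 0.50 × 0.50)]² / 0.30² = 38.5, so 39 per group. With 25 per group the power is 61%. Against a rate of 20%, 25 per group reaches 80% power only when the other arm is at 58%.

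**4. Score against remission, by simulation.** The setting is four arms, 3000 runs each, with three assumed day-10 distributions over five levels (none, IA, IB, II, III). One arm is better by a common odds ratio of 4, meaning its odds of being at or below each level are multiplied by 4. The tests are chi-square for each binary form and Kruskal-Wallis for the ordinal score. Baseline is not used. Power at 21 per arm:

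| Assumed distribution in the other arms | Remission = none | Remission = none or IA | Ordinal score |
|---|---|---|---|
| .15, .25, .25, .25, .10 | 53% | 60% | 70% |
| .30, .25, .20, .15, .10 | 61% | 48% | 66% |
| .10, .15, .30, .30, .15 | 43% | 61% | 71% |

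Across repeat runs the ranges are about 65–71% (ordinal) and 41–62% (binary) at 21 per arm, and 73–80% and 48–72% at 25.

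**5. Freedom of choice.** With an odds ratio of 1, declaring success when any of the three forms is significant gives a false-positive rate of about 9–11% instead of 5%. The standard error is √(0.10 × 0.90/3000) = 0.5 percentage points, so these rates carry a simulation error of about one point.

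**The case against.** The strongest reply is that only one variable is actually measured, namely the score, and that remission is a loose label for its reduction. The article states no responder count and no test of proportions, and the Brunner-Langer test could handle an ordered score at two visits. This stands as far as it goes: the text leans towards the score. It does not remove the defect, because the heading and aim still promise a conclusion about remission, the Brunner-Langer test is conditional on non-normality, and the sample size is on neither scale.

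A second reply is that the cited classification, or a fuller protocol, may settle how a score is read. That is possible for the scale itself. It does not cure a primary outcome to which this document assigns conflicting data types.

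Three stronger readings are tempting and are not supported:

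- A reader might infer that entry at type IB sets the trial's disease threshold, so that falling below it is remission by the trial's own rule. The inclusion criterion only limits who enters, and nothing in the article defines remission as no longer meeting it. Type IA is never named; it is implied by admitting IB.
- A reader might take the gap in remission rate between the two cut-offs as a finding. In the simulation it is simply the assumed probability of type IA.
- A reader might infer that the type I error is already inflated. The 9–11% is a worst case that requires picking the best form after the fact. The article also plans a blinded statistical analysis, with allocation withheld until it is complete. Coded arms do not fully prevent such a choice, since a four-group p-value can be seen without knowing which arm is which, but the article gives no evidence that it happened.

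**Conclusion.** The point holds in this form: the primary outcome is named as remission, measured as a score without a linking rule, and sized as a log-scale quantity. A claim about remission would not follow from the variable measured, and the 80% power cannot be attributed to it. These conclusions rest on the text alone.

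The power figures are illustrative. They depend on the assumed five-level scale, the three distributions and the odds ratio of 4, and they ignore baseline. Under them the ordinal score has more power than either binary form, and at the planned 25 per arm it at best just reaches 80%. This should be corrected; it does not by itself invalidate the design.

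**What to change.** - **Primary outcome section:** make the day-10 ordinal score, on the full scale of the cited classification, the primary variable. Compare it between arms with the baseline score taken into account by a rank-based or ordinal method; Brunner-Langer, already named, would serve. Report remission, defined as no stomatitis, as a named supportive binary outcome, and state that a residual lower type is not remission. Align the abstract's wording.
- **Sample size section:** attribute the log-scale calculation to the outcome it fits, which within this document would be the colony count. Do not claim 80% power for the primary unless it is recalculated on the ordinal scale. Dropping the word quantitative would not be enough.
- **Trial status:** date the decision and disclose it, stating how far analysis of the clinical results had gone.

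No new data are needed, because the photographs are already to be scored on this classification. The costs are the rewording, a new power statement and a disclosed amendment while analysis is under way. The small downside is that the headline becomes a shift in score rather than a remission percentage.

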#### Secondary

##### Systemic evaluation

Patients’ blood pressure will be indirectly measured by the oscillatory sphygmomanometer method using an automated device (HEM7130, Omron Healthcare Brazil, São Paulo, SP); two to three measurements will be performed with a 5-min interval, recording the systolic (maximum) and diastolic (minimum) blood pressure. The technique for obtaining and classifying the individuals will follow the categorization proposed by the American Heart Association (2019).

Patients will be referred for continuous electrocardiographic monitoring with the Einthoven’s II lead, combined with monitoring of the respiratory rate with an elastic strap holding a stretch sensor around the thorax. The electrocardiogram and the respiratory sensor signal will be filtered (100 Hz to 0.5 kHz), amplified (BioAmp ADInstruments, Bella Vista Australia), digitalized (PowerLab 2/20 ADInstruments Bella Vista, Australia) and sampled (1000 Hz) continuously, using an IBM/PC. The files with the electrocardiogram recordings will be processed using a computer program (ECG Module for LabChart, ADInstruments, Bella Vista, Australia), which identifies the QRS complex of the electrocardiogram and calculates the duration of successive intervals between R waves (RR interval or cardiac interval). This processing will allow the generation of time series, beat-to-beat, from the cardiac interval values.

Cardiac interval variability will be analyzed using these recordings (spectral analysis). The series with RR interval values will be re-sampled at 3 Hz by cubic interpolation, to regularize the interval between beats. The series with interpolated RR interval values will be divided into segments with 512 values each, with a 50% overlap. The stationarity of each segment will be examined visually, and those with artifacts or transients will be excluded. Each segment will have its spectrum calculated by fast Fourier transform (FFT) after hanning windowing. The RR range spectra will be integrated into low frequency (LF) (0.04–0.15 Hz) and high frequency (HF) (0.15–0.50 Hz) bands. The relative power (normalized units) of the RR interval spectra in each frequency band, and the ratio of the LF and HF (LF/HF) powers thereof, will be determined.

Symbolic analysis searches for patterns of changes between successive cardiac interval values, classifies these changes and quantifies their occurrence. Sequences of three symbols will then be analyzed and classified into four different families, according to the number of variations found. The frequency of occurrence of each pattern will be analyzed and indicated as 0 V%, 1 V%, and 2 V%. The frequency of variations of type 0 V (sympathetic) and 2 V (vagal) are of interest as indicators of cardiocirculatory autonomic modulation.

The sampling entropy (SampEn) will be calculated from the IC series with the help of the JBioS software. The number of practical terms, SampEn quantifies the (logarithmic) probability that near-size patterns *m* will continue to *m* + 1. In other words, of the size patterns *m* that are similar, SampEn indicates which percentage of these will remain similar for *m* + 1, that is, when an extra point is considered. High probability of the patterns continuing closely indicates regularity, yielding low values of entropy. Cardiac variability and blood pressure will be recorded in the control period and after the treatment of DS through hygiene protocols. Thus, each patient will be their own control.

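### The printed 100 Hz lower filter edge removes the respiratory signal and severely attenuates the ECG R wave on which every heart-rate-variability outcome depends

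*Protocol article*

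**What the plan says.** The setting is in the Protocol article, Study outcomes, Secondary, Systemic evaluation. One band is given for two channels: "The electrocardiogram and the respiratory sensor signal will be filtered (100 Hz to 0.5 kHz". Both signals are then amplified, digitised and "sampled (1000 Hz) continuously".

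The same paragraph gives the purpose of each channel:

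- The chest strap serves "monitoring of the respiratory rate with an elastic strap holding a stretch sensor around the thorax".
- The ECG goes to software that "identifies the QRS complex of the electrocardiogram and calculates the duration of successive intervals between R waves".

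The RR series is built from those intervals. For spectral analysis, "The series with RR interval values will be re-sampled at 3 Hz by cubic interpolation", and its spectrum is integrated into "low frequency (LF) (0.04–0.15 Hz) and high frequency (HF) (0.15–0.50 Hz) bands". The symbolic indices and sample entropy, described in the same section, also come from the cardiac-interval series. No other part of the article gives a different filter band, and the filter type and order are not stated.

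**The concern.** A band starting at 100 Hz rejects what lies below 100 Hz. Breathing is far below that, and so is most of the energy of a QRS complex. As printed, the setting therefore conflicts with the purpose given for each channel in the same paragraph.

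All HRV outcomes come from one RR series, and that series depends on finding R waves in the filtered ECG. Missed or false beats would distort LF, HF, LF/HF, the symbolic indices and sample entropy together. HRV is formally secondary, but it is the first response variable named in the Abstract, and cardiovascular risk is part of the primary null hypothesis under Study hypothesis. The article chose to state this setting, so the problem is a wrong value and not a detail left to a fuller document.

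**Working it through.** **Inputs from the article.** Lower edge 100 Hz, upper edge 0.5 kHz = 500 Hz, sampling rate 1000 Hz.

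**Assumptions, because the article gives no figure.**

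- Filter: Butterworth high-pass at 100 Hz, orders 1, 2 and 4.
- Breathing: 0.15–0.50 Hz, borrowing the article's HF limits as a guide. This is 0.15 × 60 = 9 to 0.50 × 60 = 30 breaths per minute.
- ECG: a simulated 300 s trace at 1000 Hz with sum-of-Gaussians beats, R-wave SD 6–12 ms, white noise of 0.5%, 1% or 3% of R amplitude, and a simple envelope peak detector.

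**Step 1: upper edge.** The Nyquist frequency is 1000/2 = 500 Hz. The upper edge equals it and so agrees with the sampling rate. Only the lower edge is in question.

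**Step 2: filter gain.** For order n at frequency f, gain = 1/√(1 + (100/f)^(2n)).

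| Frequency | 100/f | Order 1 | Order 2 | Order 4 |
|---|---|---|---|---|
| 0.15 Hz | 667 | 0.15% | 0.0002% | practically 0 |
| 0.50 Hz | 200 | 0.5% | 0.0025% | practically 0 |
| 10 Hz | 10 | 10% | 1% | 0.01% |
| 25 Hz | 4 | 24% | 6% | 0.4% |

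For example, at 0.50 Hz and order 1 the gain is 1/√(1 + 200²) ≈ 0.005. Below 100 Hz the gain falls as the order rises, so 0.5% is the most that breathing can keep. The respiratory trace is lost at any order.

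**Step 3: what is left of the R wave.** In the simulated ECG less than 0.0002% of the power lay above 100 Hz. Over R-wave SDs from 12 down to 6 ms, the residual R peak relative to its original height was:

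- order 1: 9–17%
- order 2: 1.7–6.7%
- order 4: 0.08–1.2%

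**Step 4: can beats still be found?** Each run had 352 or 353 true beats.

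| Order | Noise 0.5% | Noise 1% | Noise 3% |
|---|---|---|---|
| 1 | all found, none false | all found, none false | all found, none false |
| 2 | all found, none false | all found, 0 to 40 false | from 351 of 352 (31 false) down to 96 of 353 |
| 4 | 80 to 349 found, many false | 69 to 145 found, many false | 65 to 78 found, many false |

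The best order-4 run found 349 of 353 beats among 412 detections, so 412 − 349 = 63 were false. The other order-4 runs found 65 to 145.

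**Step 5: where the LF and HF bands apply.** They are bands of the RR series, which is formed after beat detection and resampled at 3 Hz. The acquisition filter does not act on that series. It can damage the bands only by causing missed, false or mistimed beats.

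**The case against.** The strongest reply is that the HRV outcomes may be sound even with the printed band. RR timing needs a detectable R wave, not a preserved waveform. With a first-order filter every beat was found at every noise level, and with a second-order filter every beat was found at low noise. The one channel that is certainly lost, respiration, feeds no listed outcome. RR segments are also inspected visually and disturbed ones dropped, so gross failure would probably be noticed. The value may simply be a misprint.

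Much of this stands, and it limits the point. It does not remove it. The order is not stated, so survival cannot be assumed. Visual inspection would turn detection errors into lost data: one segment of 512 values at 3 Hz is 512/3 ≈ 171 s of recording. A misprint is plausible, but the article can neither confirm it nor show the intended value.

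A reader might be tempted to go further, in three ways that the document does not support:

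- **That the filter removes the source of all HRV outcomes and leaves only noise.** This would need a steep filter or a noisier signal, and the article specifies neither.
- **That a 100 Hz edge deletes the 0.04–0.50 Hz bands.** Those bands belong to the RR series after beat detection.
- **That the 500 Hz upper edge is a second error.** It matches the sampling rate.

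**Conclusion.** The stated band is wrong as written for both channels, because of its 100 Hz lower edge. This takes the printed range as the pass band, which is the usual meaning.

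- **Respiration:** removed at any filter order, with gain at most 0.5%. Respiratory rate cannot be monitored as stated.
- **ECG:** severe attenuation with possible loss of beat detection. The outcome ranges from no missed beats (order 1) to most beats missed (order 4 in nearly all runs). These figures rest on the Butterworth form, the assumed R-wave widths and noise levels, and a simple detector. Real recordings and the laboratory's software may do better or worse.

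The HRV outcomes are therefore at risk and not shown to be lost. Blood pressure comes from a separate automated device, and the primary outcome is scored from palate photographs, so neither is affected. The document does not show that recordings were actually made with this band.

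**What to change.** 1. Check the acquisition settings stored with the recordings and correct the article. State the band separately for ECG and respiration, each with a lower edge that passes the signal, and give the filter type and order.
2. If the printed band was really used, verify R-wave detection against the recordings before any HRV analysis. Exclude recordings in which beats cannot be reliably detected. Make that decision without knowledge of group and report the number excluded per group. Report respiratory rate as not available.

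If the band is a misprint, the cost is one settings check and one corrected sentence. If it was used, the cost is a review of beat detection in the recordings. Trial status says clinical results are already being analysed, so the check should come before any HRV result is reported.

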##### Local parameters

To verify biofilm removal on the inner surface of the upper prosthesis, the technique described will be performed according to Badaró et al. [11], such that from the biofilm evidence, the prostheses will be photographed in standardized positions. The areas of biofilm and the surface of the prosthesis will be calculated using software and will be applied in a formula to identify the amount of total area of the biofilm, before and after treatment.

The microbial load of the prostheses and the palate will be evaluated. Biofilm at these sites will be collected according to the protocol recommended by Kabawat et al. [10] and de Souza et al. [29]. Serial dilutions will then be obtained, which will be seeded in Petri dishes with culture medium specific for the growth of *Staphylococcus* spp. (Mannitol Salt Agar, Kasvi Imp. e Dist. de Prod. para Laboratórios Ltda, Curitiba, Brazil), Gram-negative bacteria (MacConkey Agar, Himedia Laboratórios PVI Ltd., Mumbai, India), *Candida* spp. (CHROMagar™ *Candida*, Becton Dickinson, Paris, France) and *Streptococcus mutans* (SB20 Modified Agar with Casitone, Himedia Laboratories PVI Ltd., Mumbai, India)*,* and incubated in a microbiological stove (De Leo Equipamentos Laboratoriais, Porto Alegre, RS, Brazil) at 37 °C for 48 h. *S*. *mutans* will be anaerobically cultivated in a microaerophilic environment in a jar (Permution, Curitiba, PR, Brazil). After the incubation period, the CFU count will be performed to quantify the microbial load. The biological specimens present in the collected biofilm will be stored at − 80 °C for future analysis, if utilized; we will formally communicate any amendments to the protocol during the trial.

The Breath Alert™ portable device (Tanita Corporation®-Japan), used according to the manufacturer’s instructions, will measure the odor of the cavity with and without the dentures. The odor level will be given as a score determined using the apparatus, with values that can vary from 1 to 4. Thus, the odor is classified according to the scores [30] as (1) odorless, normal; (2) mild, normal odor; (3) moderate, bad breath - perceptible; or (4) strong odor, noticeable. The patient will be evaluated for odor without the prosthesis in position and then with the prosthesis seated in the oral cavity. Thus, the odor related to the prosthesis will be calculated based on the difference between the odor of the cavity with and without the prosthesis.

Saliva samples will be collected to evaluate salivary parameters. The non-stimulated total saliva will be collected for 10 min by the method of spitting, which will be analyzed for viscosity and pH measured. The calibration of pH will be performed in a pHmetro (PHTEK, Curitiba, Paraná, Brazil) after calibration of the equipment. The kinematic viscosity of saliva will be measured using a glass viscometer, and the liquid viscosity coefficient will be calculated according to Shekhar et al. [31]. The total stimulated saliva will be collected for 5 min using the habitual chewing of 1 g of gum base [19], from which the calculation of saliva volume will be obtained to evaluate the salivary flow. Subsequently, saliva samples will be centrifuged at 10,000 × g for 15 min at 4 °C, to remove cellular debris. Aliquots of supernatant will be stored at − 80 °C for the analysis. The precipitates will be evaluated by ELISA [22] to identify and quantify MUC1 expression. The absorbance at 405 nm will be measured after 30–45 min in an ELISA reader.

As a control, wells without saliva will be used. The assay for saliva will be performed in triplicate, and the results will be presented as the mean difference between optical density (OD) readings in experimental and control wells. Salivary concentrations of cytokines (IL-6 and TNF-α) will be measured using ELISA kits (Multiplex Human Cytokine Magnetic Bead Kit (Millipore, USA) according to the manufacturer’s instructions [32]. The determination of C-reactive protein in saliva will be performed using CRP ELISA kits (Salimetrics Europe Ltda.) [33]. Both ELISA methodologies will be performed in duplicates on two standard 96-well microplates, according to the protocol provided by the respective suppliers.

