**Material/design:**

A clinical trial, randomized, double-blind, and with parallel groups, will be conducted in Brazil The sample will consist of 100 patients without teeth in both arches, users of at least maxillary complete dentures, and diagnosed with DS, who will be allocated to groups (*n* = 25 per group) according to the different hygiene protocols: (1) brushing of the palate and immersion of the prosthesis in 0.25% sodium hypochlorite solution (positive control); (2) brushing of the palate and immersion of the prosthesis in 0.15% triclosan solution; (3) brushing of the palate and immersion of the prosthesis in lactose monohydrate; or (4) brushing the palate with citric acid and immersing the prosthesis in lactose monohydrate. The response variables will be heart rate variability and alteration of blood pressure (systemic level), remission of DS, removal of biofilm, reduction of microbial load (colony-forming units (CFU)), mouth and prosthesis odor level, expression of MUC1, proinflammatory cytokines, C-reactive protein (CRP), viscosity, pH and salivary flow (locally); patient-centred qualitative analysis will also be undertaken. Measurements will be performed at baseline and 10 days after the interventions. The results obtained will be statistically analyzed as pertinent, with a level of significance of 0.05.

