### Planned interventions

All patients will receive verbal and written instructions according to the hygiene protocols: they should brush the palate region with a soft toothbrush and water for 2 min, once a day (Toothbrush CS 5460C Adulto Ultra Macia, Curaprox, Curaden Swiss do Brasil Imp. Exp. LTDA, São Caetano do Sul, São Paulo, Brasil); immerse their dentures in the specific product once a day for the length of time proposed by the manufacturer; and brush the prosthesis for 2 min using a specific brush (Prosthesis Brush BDC150/152/153, Curaprox, Curaden Swiss do Brasil Imp. Exp. LTDA, São Caetano do Sul, São Paulo, Brazil) and neutral soap, three times a day. In addition, all patients will be instructed to remove the prosthesis during the night and leave it in a container with clean water, and in the morning to rinse the prosthesis under running water before inserting it into the oral cavity. Neutral soap and the solutions will be available to participants in identical dosing vials and in sufficient quantity for continuous use for 10 days; for greater control and monitoring of the hygiene protocol. citric acid in the form of an effervescent tablet will be removed from the package and placed in neutral packaging.

The parallel groups as determined by the different hygiene protocols will each consist of 25 participants. The protocols are as follows:
Group 1 (G1 (control group)) - brushing the palate with a soft brush and prosthesis immersion in 0.25% sodium hypochlorite solution (control group)Group 2 (G2) - brushing the palate with a soft brush and prosthesis immersion in 0.15% triclosan solutionGroup 3 (G3) - brushing the palate with a soft brush and prosthesis immersion in citric acid (Nitradine, Bonyf AG, Liechtenstein, Switzerland)Group 4 (G4) - prosthesis immersion and brushing of the palate with citric acid and a soft brush (Nitradine, Bonyf AG, Liechtenstein, Switzerland)

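### Prosthesis odor is a difference of two scores capped at 4, so it is truncated in patients with strong mouth odor and can rise when only the mouth improves

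*Protocol article*

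**What the plan says.** The abstract of the protocol article lists "mouth and prosthesis odor level" among the response variables and gives the time points: "Measurements will be performed at baseline and 10 days after the interventions".

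Local parameters, under the secondary outcomes, describes the measurement. "The odor level will be given as a score determined using the apparatus, with values that can vary from 1 to 4". The categories are ordered: "1) odorless, normal; (2) mild, normal odor; (3) moderate, bad breath - perceptible; or (4) strong odor, noticeable". Two readings are taken at each assessment: "The patient will be evaluated for odor without the prosthesis in position and then with the prosthesis seated in the oral cavity". The denture outcome is then derived from them: "the odor related to the prosthesis will be calculated based on the difference between the odor of the cavity with and without the prosthesis".

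The section states no sign for the subtraction, no handling of patients who already score 4 without the denture, and no separate reading of the denture itself.

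Planned interventions has all participants treat the palate as well as the denture: "they should brush the palate region with a soft toothbrush and water for 2 min, once a day". Group 4 is described as "prosthesis immersion and brushing of the palate with citric acid and a soft brush".

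**The concern.** The derived score is meant to isolate what the denture adds to mouth odor. Two features of the definition work against that.

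- **The scale has a top.** A patient whose mouth alone scores 4 has no room for the denture to register. At 3 there is room for one level only. The same denture therefore receives a different score depending on the mouth it sits in.
- **The subtracted term can respond to treatment.** Palate brushing may lower the mouth-only reading between baseline and day 10. If the with-denture reading was held at 4 by the cap, the mouth reading can fall further than the with-denture reading, and the difference rises.

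At stake is the reading of one secondary outcome. A between-arm difference in prosthesis odor could reflect how much hidden denture odor each arm uncovered, rather than how well each product cleaned the denture.

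**Working it through.** **Inputs.** The definition, the 1 to 4 range and the two readings come from Local parameters. Palate brushing in all arms comes from Planned interventions. The article gives no odor distribution, so the last step uses assumed values.

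Let O be the score without the denture, W the score with it, and D = W − O. The sign is the natural reading. With the opposite sign the results below are mirrored.

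**1. Range of D.** Since 1 ≤ W ≤ 4, D lies between 1 − O and 4 − O. If the denture truly adds two levels and the reading is cut off at 4 (an additive form that I assume), then D = min(4, O + 2) − O.

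| O | Possible D | D for a true two-level contribution |
|---|---|---|
| 1 | 0 to 3 | 2 |
| 2 | −1 to 2 | 2 |
| 3 | −2 to 1 | 1 |
| 4 | −3 to 0 | 0 |

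**2. One patient.** Baseline O = 4, W = 4 gives D = 0. Day 10 with O = 2, W = 3 gives D = +1. Both readings fall, and the derived score rises.

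**3. All possible transitions with W ≥ O.** There are 10 such score pairs, and 40 transitions between them in which neither reading worsens and at least one improves. D rises in 15, is unchanged in 10 and falls in 15. Among the 15 rises, W is unchanged in 10. Both readings improve in the other 5, and 4 of those 5 start at W = 4. These are counts of possibilities, not expected frequencies.

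**4. Illustrative size.** Assume latent mouth odor is normal with mean μ and SD σ = 0.9, the denture adds a fixed δ, and the device score steps up at 1, 2 and 3. Then

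E[D] = Σ over c = 1, 2, 3 of { Φ((c − μ)/σ) − Φ((c − δ − μ)/σ) }.

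| μ | δ | Terms for c = 1, 2, 3 | E[D] |
|---|---|---|---|
| 3.0 | 0.90 | 0.0125 + 0.1159 + 0.3413 | 0.47 |
| 2.0 | 0.90 | 0.1159 + 0.3413 + 0.3225 | 0.78 |
| 1.0 | 0.90 | 0.3413 + 0.3225 + 0.0977 | 0.76 |
| 3.0 | 0.45 | 0.0099 + 0.0797 + 0.1915 | 0.28 |
| 2.0 | 0.45 | 0.0797 + 0.1915 + 0.1373 | 0.41 |

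Reading the table:

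- Baseline mean 3.0, mouth falls by one unit, denture unchanged: 0.47 to 0.78, an apparent worsening.
- Baseline mean 2.0, same fall: 0.78 to 0.76, practically nothing.
- Baseline mean 3.0, denture contribution halved: 0.47 to 0.28 if the mouth is unchanged (a drop of 0.19), but 0.47 to 0.41 if the mouth also falls by one unit (a drop of 0.06). The direction is right and most of the benefit is lost.

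The assumption behind the first case is severe. At μ = 3.0, 50% of patients score 4 without the denture and 87% score 3 or 4. At μ = 2.0, 50% score 3 or 4 and 13% score 4.

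**The case against.** The strongest reply is that the score does what it says. It is the denture's increment over the mouth, not total odor, and mouth odor is listed as a quantity of its own. If the mouth improves and the with-denture reading does not, a larger denture share is the correct answer. That covers 10 of the 15 rises in step 3, apart from the ceiling. In the 4/4 to 2/3 example the baseline denture contribution is hidden by the cap, so nobody can say that a real improvement in denture odor was reversed. This stands. It means that the defect is mainly the ceiling, and not a separate fault of direction.

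A reader might infer from step 3 that the outcome records 15 of 40, or 38%, of improved patients as worse. The article does not support that. The count gives every score pair equal weight, and no score distribution is reported.

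A reader might also infer that the outcome is biased against Group 4, which applies its product to the palate, in the comparison with Group 3. That is not shown either. A fall in mouth odor enters both readings and largely cancels away from the ceiling, so any distortion of that contrast depends on the same unknown baseline scores. The eligibility criteria do not select for bad breath, so a baseline as severe as μ = 3.0 cannot be presumed.

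What the reply does not remove is the cap itself. It follows from the stated definition, and the derived score cannot distinguish denture odor that has been uncovered from denture odor that has increased.

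**Conclusion.** The point holds in a limited form. As defined, prosthesis odor cannot exceed 4 minus the mouth-only score: no positive value at 4, at most +1 at 3. A fall in mouth odor can therefore raise it with no change in the denture. This is arithmetic and needs no assumption beyond the sign convention.

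The practical size is unknown. It is large if many patients start at 3 or 4 (0.47 to 0.78 in the illustration with latent mean 3.0) and negligible at a lower baseline (0.78 to 0.76 at 2.0). Those figures rest on an assumed normal latent odor with SD 0.9, a fixed denture contribution of 0.9 and cut-points at 1, 2 and 3. Where denture odor really falls by half, the illustration shows attenuation and not reversal.

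The point concerns one derived secondary outcome. The primary outcome and the sample size are unaffected, and both raw readings should be available.

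**What to change.** Analyse the two readings as separate ordinal outcomes, odor without the denture and odor with the denture in place. Compare each between arms with its own baseline score in the model.

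If the difference is kept, fix its sign, label it descriptive, tabulate it by baseline mouth-only score and state the ceiling beside the table. For the between-arm comparison, do not adjust for the day-10 score without the denture and do not exclude patients because of it. That score is measured after randomization and may itself be affected by treatment, so conditioning on it could introduce a new bias.

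The cost is the wording of one outcome definition and one analysis line. No new visits or measurements are needed. The downside is timing: Trial status says that clinical results are already being analysed. The change should therefore be recorded with a date, made while the analyst is still blinded as described under Randomization, allocation, and blinding, and disclosed in the report, with the difference defined in the protocol also shown.
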